### Renal hemodynamic calculation

mGFR and effective renal plasma flow (eRPF) will be calculated using inulin and PAH clearance, respectively. Briefly, 1% inulin and 0.5% PAH will be administered by means of a continuous intravenous infusion for 2 h under overnight fasting but hydrated conditions. If the participants are prescribed diabetic drugs and diuretics, they will be instructed to suspend the use of these drugs. Before infusion, participants will drink 500 ml of tap water in the outpatient treatment room to stimulate diuresis. During infusion, blood samples will be drawn 2 times at 45 and 105 min for measurement of serum levels of inulin and PAH, and urine samples will be collected between 45 and 105 min for measurement of urinary inulin and PAH excretion after completely emptying the bladder 45 min after the start of the infusion.

The filtration fraction (FF), effective renal blood flow (eRBF), and renal vascular resistance (RVR) will be calculated by dividing mGFR by eRPF, eRPF by (1-hematocrit), and mean blood pressure by eRBF, respectively. eGFR from creatinine levels (eGFRcreat) will be calculated as follows: eGFRcreat (mL/min/1.73 m^2^) = 194 × SCr^−1.094^ × Age^−0.287^ (× 0.739: coefficient for female) [12].

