### Endpoints

The primary endpoint of the protocol is the percentage change in FF after 4 weeks of treatment in the canagliflozin and control groups. The secondary endpoints are (1) the change in FF, percentage change, and change in (2) mGFR, (3) eRPF, (4) eRBF, and (5) RVR after 4 weeks of treatment; (6) changes in eGFR, HbA1c, and albuminuria after 4 and 12 weeks of treatment; and (7) trend of blood pressure and body weight after 4 and 12 weeks of treatment in the canagliflozin and control groups. In addition, we plan to (8) compare the changes in urinary angiotensinogen levels between the canagliflozin and control groups after 4 weeks of treatment. Moreover, the rate of adverse drug reactions will be assessed for safety.

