### Sample size

For the purpose of comparing independent results, we decided to use power of 0.85 and a significance level of 0.05, to detect a significant difference. The difference in the percentage change in FF after 4 weeks of treatment in the canagliflozin group compared with that in control group was assumed to be 60% of the standard deviation. Based on these calculations, we determined that at least 50 individuals are necessary for each group. Taking into account potential discontinuation and withdrawal, we set the target number for the canagliflozin group to 55, with 55 control patients, and thus, 110 patients were planned to be included in total. Additionally, we took into account the actual number of patients who met the registration criteria at each facility.

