### Statistical analyses

Validity/safety will be analyzed in the largest analysis target group (full analysis set; FAS), defined below. To be included in the FAS, subjects must satisfy these two criteria: (1) meet the selection criteria and not meet the exclusion criteria, and (2) have at least one marker to evaluate efficacy after administration (regardless of the primary or secondary endpoint). The primary aim of the analysis is to compare the percentage changes between the canagliflozin group and the control group at 4 weeks after administration using analysis of covariance (ANCOVA) with eGFR, proteinuria, age, and HbA1c as covariates. No interim analysis is planned.

The analysis methods for secondary outcomes are shown in Table 2.

**Table 2 Tab2:** Analysis methods for secondary outcomes of the canagliflozin and control groups

Secondary outcomes	The analysis methods
1. Percentage change and the change in eRPF, eRBF, and RVR after 4 weeks of treatment	• Compare the percentage changes between the canagliflozin group and the control group at 4 weeks after administration by analysis of covariance (ANCOVA) with eGFR, proteinuria, age and HbA1c as covariates
2. Change in FF, eRPF, eRBF, and RVR after 4 weeks of treatment	• Compare the percentage changes between the canagliflozin group and the control group at 4 weeks after administration by analysis of covariance (ANCOVA) with FF, eRPF, eRBF, and RVR at the baseline and eGFR, proteinuria, age, and HbA1c as covariates
3. Changes in eGFR, HbA1c, albuminuria after 4 weeks and 12 weeks of treatment, trend of blood pressure and body weight after 4 weeks and 12 weeks of treatment, and change in urinary angiotensinogen levels after 4 weeks of treatment	• Calculate the adjusted mean and the 95% CI for changes at each time point by a linear mixed model with each treatment group, time point, and interaction of the treatment group and time point as the fixed effects • Compare between treatment groups using a linear mixed model with values of each index at baseline, treatment groups, time points, interaction between treatment groups and time points as the fixed effects and changes of each index as response variables • Compare changes of each index among treatment groups at each time point using the Tukey–Kramer method to correct for multiplicity
4. Rate of adverse drug reactions	• Calculate the 95% confidence interval for each treatment group and compare it between the groups using χ2 test (or Fisher's exact test)

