
The possible renal protective effects of SGLT2i are diverse, including lowering blood pressure via natriuresis and osmotic diuresis, reducing hypoxia in the proximal tubule via tubular workload reduction, and anti-inflammation-fibrosis action [20–22]. Among these actions of SGLT2i, correction of intraglomerular hypertension via restoration of tubular glomerular feedback is thought to be the most crucial and dynamic [21]. An experimental study in an animal model of type 1 diabetes demonstrated that SGLT2i induced afferent arteriolar vasoconstriction and decreased the single-nephron glomerular filtration rate via the tubule-glomerular feedback mechanism that resulted in the reduction of intraglomerular pressure, using in vivo multiphoton microscopy imaging techniques [23]. Cherney et al. demonstrated that SGLT2i attenuated glomerular hyperfiltration in patients with type 1 diabetes mellitus with glomerular hyperfiltration defined by eGFR ≥ 135 mL/min/1.73 m^2^; attenuation of glomerular hyperfiltration was accompanied by a decrease in renal blood flow and an increase in renal vascular resistance [10]. The authors discussed that such a reduction of glomerular hyperfiltration was mediated by preglomerular vasoconstriction by affecting the tubular-glomerular feedback mechanism, and long-term use of SGLT2i might reduce intraglomerular pressure, resulting in an overt renoprotective effect [10]. Interestingly, this trial failed to show this evidence in patients with normal glomerular filtration [10]. Recently, van Bommel et al. conducted a trial to evaluate the renal hemodynamic effect of SGLT2i in patients with type 2 diabetes mellitus with eGFR ≥ 60 mL/min/1.73m^2^ treated with metformin monotherapy [11]. They showed that SGLT2i lowered the mGFR without increasing renal vascular resistance, and these effects were accompanied by postglomerular vasodilation [11]. Interestingly, the ability to lower postglomerular resistance was independent of blood glucose concentration [11]. Although clinical studies have demonstrated a renoprotective effect of SGLT2i in patients with type 2 diabetes who have moderate renal dysfunction, as discussed above, changes in renal hemodynamics after SGLT2i administration in these patients are still unclear. This trial will contribute to research in the field by elucidating the renal hemodynamic mechanism of SGLT2i and, provide a significant basis for the prescription of SGLT2i in patients with DKD if we demonstrate its ability to control intraglomerular pressure in our subjects.

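### The primary FF analysis and Table 2 row 1 use raw percentage change without the variable's own baseline: the between-arm test is valid, but arm-level means are inflated and some precision is lost

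*Protocol article*

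**What the plan says.** The protocol article (Endpoints) makes the 4-week percentage change in FF the primary endpoint. Among the secondary endpoints it lists absolute change in FF, and "percentage change, and change in (2) mGFR, (3) eRPF, (4) eRBF, and (5) RVR after 4 weeks of treatment".

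Under Statistical analyses, the primary aim is to "compare the percentage changes between the canagliflozin group and the control group at 4 weeks after administration using analysis of covariance (ANCOVA"). The covariates are eGFR, proteinuria, age and HbA1c. Table 2 row 1 repeats that model for eRPF, eRBF and RVR. Baseline FF is not in the primary model, and the baseline of the analysed variable is not in row 1. Row 2 does include these baselines. No log scale is mentioned.

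FF, eRBF and RVR are derived quantities. Under Renal hemodynamic calculation they "will be calculated by dividing mGFR by eRPF, eRPF by (1-hematocrit), and mean blood pressure by eRBF, respectively".

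**The concern.** A percentage change divides by a baseline that is itself measured with error. Here each clearance rests on one timed urine collection and two blood samples. The ratio week 4/baseline is right-skewed, so its arithmetic mean exceeds 1 even when nothing has changed. RVR is pressure divided by eRBF, so the same error pushes the mean percentage change of both upward.

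This matters for interpretation. The Discussion separates mechanisms by the direction of flow and resistance. In one earlier study, "attenuation of glomerular hyperfiltration was accompanied by a decrease in renal blood flow and an increase in renal vascular resistance"; in another, mGFR fell without a rise in resistance. Arm-level percentage changes read on their own could blur that contrast.

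The second issue is efficiency. A change score that is not adjusted for its own baseline carries avoidable noise, and a right-skewed response gives extra weight to patients with a low baseline test.

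**Working it through.** **The plan's own figure.** Sample size states "power of 0.85 and a significance level of 0.05", and a difference that "was assumed to be 60% of the standard deviation". Two-sided, n = 2(1.960 + 1.036)²/0.6² = 49.9, so 50 per arm. This reproduces "at least 50 individuals are necessary for each group". Power at 50 is 0.851 by the normal formula and 0.844 by the noncentral t. The sample size is not in question.

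The documents give no SD for any hemodynamic measure. Every variability below is therefore an assumption, on the log scale, with log-normal variation.

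**1. Arm-level offset.** With no true change and s the SD of ln(week 4/baseline), the mean percentage change is 100 × (exp(s²/2) − 1).

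| s | 0.10 | 0.15 | 0.20 | 0.25 | 0.30 |
|---|---|---|---|---|---|
| Spurious mean change | +0.5% | +1.1% | +2.0% | +3.2% | +4.6% |

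**2. eRBF and RVR together.** Let visit-to-visit SD be σ, so s² = 2σ², and let mean blood pressure have an assumed visit SD of 0.06. At σ = 0.10, eRBF gives exp(0.0200/2) − 1 = +1.0% and RVR gives exp(0.0272/2) − 1 = +1.4%. At σ = 0.15 they are +2.3% and +2.6%; at σ = 0.20, +4.1% and +4.5%. Nothing has changed in any of these cases.

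**3. Between arms.** Both arms share the offset. In simulation (50 per arm, 4,000 replicates per setting) the planned model's mean difference under no effect was within about 0.1 percentage point of zero, and type I error was 0.045 to 0.058. A true effect is multiplied by exp(s²/2): −8.2 against a true −8.1 points at σ = 0.10, and about −16.3 against −15.6 at σ = 0.20.

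An example shows both sides. Take a true 5% fall in mGFR with eRPF unchanged, and most error coming from the shared urine volume.

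| | mGFR | eRPF | FF |
|---|---|---|---|
| Treated arm | −1.8% | +3.4% | −4.3% |
| Unchanged control arm | +3.4% | +3.4% | +0.7% |
| Difference (points) | −5.2 | 0 | −5.0 |

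The treated arm alone misleads; the difference does not. The FF offset of 0.7% corresponds to s of about 0.12, because urine-volume error cancels in mGFR/eRPF.

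**4. Power.** The true effect is 0.6 SD of the log ratio. The models contain four covariates, one of them correlated 0.3 with the patient's true level. τ is the between-patient log SD.

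| σ (s) | τ | % change, no baseline (planned) | Log ratio, no baseline | % change + baseline | Log ratio + baseline |
|---|---|---|---|---|---|
| 0.05 (0.07) | 0.25 | 0.831 | 0.831 | 0.834 | 0.835 |
| 0.10 (0.14) | 0.25 | 0.832 | 0.833 | 0.858 | 0.860 |
| 0.15 (0.21) | 0.25 | 0.830 | 0.838 | 0.872 | 0.882 |
| 0.20 (0.28) | 0.25 | 0.816 | 0.832 | 0.896 | 0.902 |
| 0.20 (0.28) | 0.15 | 0.811 | 0.827 | 0.930 | 0.941 |
| 0.25 (0.35) | 0.15 | 0.794 | 0.820 | 0.934 | 0.954 |

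Adding baseline to the percentage model gains 0.3 to 8.0 points at τ = 0.25, and 11.9 to 14.0 in the last two rows. Changing only the scale gains 0 to 1.6 points up to s = 0.28, and 2.6 at s = 0.35.

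The closed form agrees. Baseline adjustment multiplies the variance of the log ratio by (1 + ρ)/2, with ρ = τ²/(τ² + σ²). At σ = 0.15 and τ = 0.25, ρ = 0.735 and the factor is 0.868. The standardised effect becomes 0.6/√0.868 = 0.644, and power is Φ(0.644 × 5 − 1.96) = 0.896 against 0.851, a gain of 4.5 points.

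**5. Gross errors.** Suppose 5% of tests carry an extra log SD of 0.5, with baseline in both models and τ = 0.25. Power is 0.565 on the percentage scale against 0.617 on the log scale at s = 0.15, 0.731 against 0.803 at s = 0.25, and 0.787 against 0.865 at s = 0.30. That is about 5 to 8 points.

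**The case against.** The strongest reply is that the plan compares arms. No within-arm test of a hemodynamic percentage change is stated, and the Discussion only summarises earlier studies. This stands. A reader might infer that the primary comparison is biased or its type I error inflated, but the stated analysis is a randomised between-arm comparison in which the shared offset cancels. Setting the arm-level offset against the planned 0.6-SD difference would compare unlike quantities.

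It is also true that FF probably sits at the low end of the range, so the larger offsets belong to the clearances, eRBF and RVR. A reader might further blame the percentage scale for the lost power. The figures do not support that: the missing baseline covariate accounts for most of it. The simulations are log-normal, which favours the log model, and the gross-error rate is invented.

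Finally, percentage change is a legitimate endpoint, the trial is open-label, and 81 of 110 patients had been enrolled by June 2022. A new response scale therefore alters the primary summary and is more than a change of wording. A log-scale sensitivity analysis may also exist in a document not shown. These points argue for an early, documented change that retains the raw analysis. They do not remove the case for it, because the primary response and covariates are stated here.

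**Conclusion.** The point holds as an improvement to a valid analysis. The planned test is not invalid, and the sample size is correct. Arm-level mean percentage changes are inflated by about 0.5% to 4.6% for s from 0.10 to 0.30, and eRBF and RVR can both read positive with no change. Omitting the variable's own baseline costs about 1 to 8 power points if the between-patient log SD is 0.25, and up to 14 if patients differ less and tests vary more. The log scale by itself adds about 0 to 2 points on clean data, and more only if some tests carry gross error.

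All sizes rest on assumed log-normal variability. Cancellation also assumes the same spread of log ratios in both arms, which holds when treatment has no effect. Absolute-change endpoints do not have the baseline-denominator inflation, so the point does not extend to them.

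**What to change.** Before database lock, and without looking at results by arm, specify for FF, mGFR, eRPF, eRBF and RVR:

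- response ln(week 4/baseline), with the planned covariates plus the log baseline of the same variable;
- 100 × (exp(estimate) − 1) with 95% CI, for each arm and for the between-arm contrast;
- the identities ln FF = ln mGFR − ln eRPF and ln RVR = ln mean blood pressure − ln eRBF as the basis for reading the components together;
- the raw percentage-change ANCOVA as a sensitivity analysis.

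Name mGFR explicitly, since Table 2 rows 1 and 2 omit it. Separately, reconcile row 2, whose label is absolute change but whose method text refers to percentage changes.

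No new data are needed. The cost is a documented change to the primary model, and a geometric-mean percentage change that needs one explanatory sentence. If the raw percentage response must stay primary, adding the variable's own baseline to that model still captures most of the power gain, but the arm-level inflation remains.

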### Enrollment, randomization, and intervention

Participant recruitment has started in December 2020 at Nagoya University Hospital, Kasugai Municipal Hospital and Nagoya Kyoritsu Hospital in the Aichi Prefecture, Japan. The inclusion, exclusion, and termination criteria are listed in Table 1. Patients are being enrolled via a web-based registration and follow-up system organized by the Nagoya University Hospital’s Center for Advanced Medical and Clinical Research, Aichi, Japan. We are randomly allocating patients to two groups: the patients of canagliflozin (100 mg/day) group will receive the trial drug in the morning added to the patients’ usual treatment and the patients of control group will continue the conservative therapy. The allocation ratio is 1:1, and a dynamic allocation strategy using a minimization method is being used. The stratifying factors for randomization are eGFR (> 45 or ≤ 45 mL/min/1.73 m^2^), proteinuria (> 0.5 or ≤ 0.5 g/g Cr), age (> 70 or ≤ 70 years), HbA1c (> 7.0 or ≤ 7.0%), and the trial site.

**Table1 Tab1:** Eligibility criteria

Inclusion criteria
**1.** Stable type 2 diabetes
**2.** eGFR (creatinine) ≤ 60 mL/min/1.73m^2^
**3.** Use of renin angiotensin system inhibitors (exclude intolerable or non-adaptive)
**4.** Age ≥ 18 years
**5.** Provision of written informed consent
Exclusion criteria
**1.** SGLT2 inhibitors administered within 8 weeks before providing informed consent
**2.** eGFR(creatinine) < 30 mL/min/1.73m^2^
**3.** Maintenance dialysis therapy or history of kidney plantation
**4.** Use of diuretics
**5.** Use of both ACEi and ARB (renin inhibitor)
**6.** Active nephritis or kidney disease
**7.** Signs of steroid diabetes
**8.** ALT and AST levels exceeding the facility standard value 2.0 fold
**9.** Heart failure NYHA class 4
**10.** Pregnant or planning pregnancy
**11.** Unsuitable for participation as assessed by attending investigator
Stop criteria
**1.** Withdrawal of consent
**2.** eGFR is dropping below 30 ml/min/1.73 m^2^ and medical decision to discontinue
**3.** Hypoglycemic symptoms and medical decision to discontinue
**4.** Ketoacidosis
**5.** Failure to attend hospital visits
**6.** Patient is found to be ineligible after starting per protocol treatment

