### Intervention and control

Eligible participants will be randomly assigned (1:1) to the canagliflozin or control group. After a run-in period of up to 4–8 weeks, the canagliflozin group patients will be administered canagliflozin 100 mg orally once daily in the morning for 12 weeks. In contrast, in the control group, glucose levels will be controlled without any SGLT2i. Inulin and para-aminohippuric acid (PAH) clearance tests for the measurement of renal hemodynamics will be performed at baseline and 4 weeks after the start of the trial. A change in the type or dose of prior diabetic drugs and antihypertensive drugs is prohibited during the 12-week intervention period, but if side effects such as hypoglycemia and hypotension occur, reduction of the dose or discontinuation of these drugs is allowed. The use of the following drugs is restricted during the 12-week intervention period: diuretics, drugs that enhance the hypoglycemic effect, including β-blockers, salicylic acid agents, and monoamine oxidase inhibitors.

The study flowchart is shown in Fig. 1.

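### The primary ANCOVA of percentage change in FF omits baseline FF: a valid analysis that gives up precision, and Table 2 rows 1 and 2 need reconciling

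*Protocol article*

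**What the plan says.** Under Endpoints, the protocol article states: "The primary endpoint of the protocol is the percentage change in FF after 4 weeks of treatment". Under Statistical analyses, the two arms are compared on percentage change at week 4 "using analysis of covariance (ANCOVA) with eGFR, proteinuria, age, and HbA1c as covariates". The covariates are listed in full, and nothing elsewhere in the article adds baseline FF to this model. They are the minimisation factors other than trial site (Enrollment, randomization, and intervention).

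Table 2 treats baseline in different ways:

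- **Row 1** (percentage change and change in eRPF, eRBF and RVR) uses the same four covariates as the primary model, without the outcome's own baseline.
- **Row 2** (change in FF, eRPF, eRBF and RVR) uses ANCOVA "with FF, eRPF, eRBF, and RVR at the baseline and eGFR, proteinuria, age, and HbA1c as covariates".
- **Row 3** (eGFR, HbA1c, albuminuria, blood pressure, body weight, urinary angiotensinogen) includes each index's baseline value in the mixed model used to compare the arms.

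Baseline FF is available for every patient who is tested as scheduled, because the inulin and PAH clearance tests "will be performed at baseline and 4 weeks after the start of the trial".

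**The concern.** The primary response is 100 × (FF at week 4 − FF at baseline) / FF at baseline. Dividing by baseline does not make the result independent of baseline. Unless FF is almost perfectly reproducible between visits, patients with a high baseline tend to show a fall and those with a low baseline a rise. A covariate that explains part of the response and is already measured has therefore been left out. eGFR is only a partial substitute for it.

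Baseline FF is not a minimisation factor, so its balance between arms is left largely to chance. At stake are the width of the primary confidence interval, the power, and how far the estimate in this one trial depends on how baseline FF happened to fall between the arms.

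There is also a question of consistency. Row 2 is titled for absolute change, but its method text describes a comparison of percentage changes, with baseline FF as a covariate. Read literally, percentage change in FF has two models, one with baseline FF and one without. Absolute change in eRPF, eRBF and RVR falls under both row 1 and row 2, with different covariates. In an open-label trial, the choice between such models should not be left until the data have been seen.

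**Working it through.** **Inputs from the article (Sample size).** "we decided to use power of 0.85 and a significance level of 0.05"; the difference "was assumed to be 60% of the standard deviation"; at least 50 per arm, 55 enrolled. Sidedness is not stated.

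**Reproducing the plan's figure.** n per arm = 2(z₀.₉₇₅ + z₀.₈₅)² / 0.6² = 2(1.960 + 1.036)² / 0.36 = 49.9, so 50. A one-sided test would give 40, so the plan is two-sided. Normal-approximation power at 50 per arm is 0.851. The t-based version gives 0.844, and 51 per arm for 85%, which is close enough. The calculation reproduces with no allowance for gain from covariates.

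**Assumption needed.** Let ρ be the correlation of FF at baseline with FF at week 4. The article does not give it, so I show 0.3, 0.5, 0.7 and 0.9, assuming equal SDs at the two visits.

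**Step 1: correlation r of percentage change with baseline FF.** In simulated data with an FF coefficient of variation of 15% or 25%, r is about −0.60, −0.51, −0.40 and −0.23 at the four values of ρ.

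**Step 2: precision.** If no other covariate carries information on FF, adding baseline FF multiplies the residual SD by √(1 − r²). At 50 per arm the unadjusted signal is 0.6 × √(50/2) = 3.0 standard errors, so power is about Φ(3.0/√(1 − r²) − 1.96). The simulations of trials with 50 per arm keep eGFR and three other covariates in both models.

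| ρ (assumed) | r | √(1 − r²) | SE ratio, simulated | Power by formula | Power, simulated |
|---|---|---|---|---|---|
| 0.3 | −0.60 | 0.80 | about 0.81 | 0.96 | about 0.96 |
| 0.5 | −0.51 | 0.86 | about 0.87 | 0.94 | about 0.93 |
| 0.7 | −0.40 | 0.92 | about 0.92 | 0.91 | about 0.89 |
| 0.9 | −0.23 | 0.97 | about 0.98 | 0.87 | 0.85-0.86 |

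The comparator is about 0.85 for the planned model. Across simulation settings the planned model's power ran from 0.81 to 0.86, so single power points should not be over-read. At ρ = 0.9 the gain within each setting is only 1-2 points.

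**Step 3: does eGFR already do the job?** With eGFR correlated 0.5 with baseline FF, the SE ratios are 0.84, 0.89, 0.94 and 0.98. With no correlation they are 0.80, 0.86, 0.91-0.92 and 0.97-0.98. eGFR recovers only a little.

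**Step 4: sensitivity to a chance imbalance.** One standard error of the baseline difference is √(2/50) = 0.2 SD. It shifts an estimate not adjusted for baseline FF by 0.2|r| SD of percentage change, or 0.2|r|/0.6 = |r|/3 of the planned effect: about 20%, 17%, 13% and 8% at the four values of ρ.

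**Step 5: is the planned estimator biased?** No. Averaged over simulated randomisations, its mean is 0.99-1.01 of the true difference.

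**The case against.** The strongest reply is that nothing in the primary analysis is broken. Randomisation gives both arms the same expected regression to the mean. The estimator is unbiased and the type I error valid. The sample size claims no covariate gain, so the trial has its stated power as written. Adjusting for the allocation factors is accepted practice. All of this stands.

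A reader might infer that the primary result is biased by regression to the mean. The document does not support that. The shift in step 4 is conditional on an imbalance that happens to occur, and it is already reflected in the wider standard error of the planned model. It is the same loss as in step 2 seen from another side, and the two must not be added together.

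A reader might also infer that FF must be noisy because it rests on one 60-minute collection. The article gives no repeatability figure. Moreover, one urine collection supplies both clearances, so urine volume and collection time cancel when mGFR is divided by eRPF. Assay error and biological variation remain, but the document does not size them. The range over ρ has to carry the argument, including 0.9, where the gain nearly vanishes.

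Row 2's reference to percentage changes may be a copying slip. If it is meant literally, a baseline-adjusted analysis of percentage change in FF is already planned as secondary. The sponsor still has to say which reading applies. Some difference between primary and secondary FF results would be expected anyway, because relative and absolute change are different scales.

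**Conclusion.** The point holds as a recommendation on efficiency, robustness and consistency. The primary model leaves out a measured covariate that is correlated with its own response, while Table 2 rows 2 and 3 adjust for the outcome's baseline. The benefit of adding it runs from substantial (standard error about 19% smaller at ρ = 0.3) through moderate (about 8% smaller at 0.7) to negligible (about 2% smaller at 0.9). These figures assume equal SDs at the two visits, a constant treatment effect on percentage change, 50 evaluable patients per arm and the planned 0.6 SD. The true ρ is unknown from the document.

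It would be too strong to call the primary analysis invalid, biased or underpowered: the stated 50 per arm reproduces and the planned test is sound. The overlap between Table 2 rows 1 and 2 is a textual inconsistency and does not depend on ρ.

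**What to change.** - Add baseline FF as a continuous covariate to the primary ANCOVA, beside eGFR, proteinuria, age and HbA1c.
- Add each variable's own baseline to the Table 2 row 1 models for eRPF, eRBF and RVR.
- Reconcile rows 1 and 2: state whether row 2 analyses absolute or percentage change, and list absolute change in eRPF, eRBF and RVR once, with one covariate set.
- Record the change, with its date, before the data are analysed. This matters because the trial is open-label and 81 of 110 patients had been enrolled by the end of June 2022. No interim analysis is planned, so no scheduled comparison stands in the way.

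The endpoint and the sample size stay as they are. The cost is one degree of freedom per model and a documented amendment to a board-approved protocol. No new measurement is needed.

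### Secondary outcomes in Table 2, row 3: arm means and 95% CIs come from a mixed model without the baseline value, while the between-group comparison uses one with it, and neither carries the minimisation factors

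*Protocol article*

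**What the plan says.** Row 3 of Table 2 (protocol article, Statistical analyses) covers the changes in eGFR, HbA1c and albuminuria and the trends in blood pressure and body weight at weeks 4 and 12, together with the "change in urinary angiotensinogen levels after 4 weeks of treatment". It has three bullets.

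- The first is the estimation step: "Calculate the adjusted mean and the 95% CI for changes at each time point by a linear mixed model with each treatment group". The list of terms ends with "time point, and interaction of the treatment group and time point as the fixed effects". No baseline value appears.
- The second is the comparison step: "Compare between treatment groups using a linear mixed model with values of each index at baseline, treatment groups, time points" and the group-by-time interaction, with "changes of each index as response variables".
- The third applies Tukey–Kramer comparisons at each time point and names no model.

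Nothing in the row labels the first model as descriptive or says which model supplies the reported difference and its CI.

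Elsewhere the plan adjusts differently. The primary endpoint is compared "using analysis of covariance (ANCOVA) with eGFR, proteinuria, age, and HbA1c as covariates". Row 1 of Table 2 uses the same four covariates, and row 2 adds the baseline value of the outcome to them. The section on enrolment and randomisation lists these four variables, with trial site, as the minimisation factors.

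**The concern.** The row describes its means as adjusted, but the model behind them contains nothing to adjust for. The same outcomes are then compared in a model that does adjust, for the baseline value. A results table built to this wording would show arm means from one model beside a comparison from another. When the arms differ by chance at baseline, the gap between the printed means will not equal the difference being tested.

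The arm means are also what readers will use to judge the eGFR dip, which the Discussion makes central to the trial's purpose, and the changes in albuminuria and blood pressure. Adjustment for the four minimisation factors, applied to the primary endpoint and to rows 1 and 2, is dropped in row 3.

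**Working it through.** **The plan's own figure.** The Sample size section gives 0.85 power, a 0.05 significance level and a difference of 0.6 SD. Taken as two-sided, n per arm = 2 × (1.960 + 1.036)² / 0.6² = 49.9, so 50, as stated. This point disputes no stated number; 50 per arm is used only as an input below.

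**What the first model returns.** With group, time and their interaction, each group-by-time cell has its own mean. With complete data, the fitted mean change in a cell is the raw mean change. The first bullet does not name its response. If raw values with baseline as a time point were meant, the change contrasts with complete data would be the same.

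**Assumptions for the size.** One time point, complete data, equal arms, baseline and follow-up variances both 1, and correlation ρ. The document gives no ρ, so a range is shown.

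**Arm means.** Write the change as (ρ − 1) × baseline + residual, with residual variance 1 − ρ².

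- Raw mean change: variance × n = 2(1 − ρ).
- Mean adjusted to the pooled baseline of both arms: variance × n = (1 − ρ²) + (1 − ρ)²/2.

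**Difference between arms.** Without baseline the variance is proportional to 2(1 − ρ); with baseline, to 1 − ρ². The SE ratio (adjusted to unadjusted) is √((1 + ρ)/2).

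| ρ | Arm mean, raw | Arm mean, adjusted | SE ratio (adj/raw) | Raw SE larger by | Difference: SE ratio | Baseline-free CI wider by |
|---|---|---|---|---|---|---|
| 0.5 | 1.000 | 0.750 + 0.125 = 0.875 | 0.935 | 6.9% | 0.866 | 15.5% |
| 0.8 | 0.400 | 0.360 + 0.020 = 0.380 | 0.975 | 2.6% | 0.949 | 5.4% |
| 0.9 | 0.200 | 0.190 + 0.005 = 0.195 | 0.987 | 1.3% | 0.975 | 2.6% |

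Seen from the other side, the adjusted arm mean has an SE about 6.5%, 2.5% and 1.3% smaller.

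**How far the two results can part.** The raw and adjusted differences differ by (1 − ρ) × the baseline difference. Under simple randomisation with 50 per arm, the SD of the baseline difference is √(2/50) = 0.20 outcome SDs. The typical gap is therefore 0.10 SD at ρ = 0.5, 0.04 at 0.8 and 0.02 at 0.9. Relative to the unadjusted SE, √(2(1 − ρ) × 2/50), that is 0.50, 0.32 and 0.22 of an SE. Minimisation on eGFR and HbA1c categories should make it smaller for those two indices.

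**What adjustment does not do.** With equal arms, the adjustment moves the two arm means by equal and opposite amounts, so their average is unchanged. Only the part due to chance baseline imbalance is removed.

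**Urinary angiotensinogen.** Its only post-baseline value is at week 4, so the time and interaction terms have no content for it.

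**The case against.** The strongest reply is that the first bullet is a within-arm summary and the second is the planned comparison. The comparison is already baseline-adjusted, and a mixed model yields a difference, a CI and a p-value together. Nothing confines it to a p-value. This stands. A reader might infer that the plan tests the treatment effect in one model and takes its estimate and CI from the other, so that significance could contradict itself. The text does not say so: the first bullet concerns mean changes and does not name an interval for the between-group difference. Figures for lost power, or for how often the two models disagree at the 0.05 level, would describe a between-group test that the plan does not contain.

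A reader might also infer that the baseline-free means are biased by regression to the mean, or that their intervals are invalid. Neither follows. Regression to the mean common to both arms stays in the adjusted means too, and in the difference it cancels in expectation under either model. The unadjusted interval has correct coverage for a within-arm mean change.

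Three smaller points have some force. For eGFR and HbA1c, the baseline value in the second model is itself a minimisation factor. For stable indices such as body weight, ρ is likely to be high and the loss slight. And an article condenses its protocol, so the choice of model for the results tables could be settled in an analysis plan that is not shown. The last does not dispose of the point, because the article does not leave the models open: it states the terms of both.

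**Conclusion.** The point holds as an inconsistency in a stated model choice, limited to the secondary outcomes in row 3. The arm means are called adjusted but are raw when data are complete, they need not agree with the planned comparison, and they are less precise by about 7% in SE at ρ = 0.5, 2.6% at 0.8 and 1.3% at 0.9. The wider CI of 15.5%, 5.4% or 2.6% applies only if their difference is read as the treatment effect. These sizes rest on equal variances, complete data, a single time point and assumed correlations.

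Omitting eGFR, proteinuria, age and HbA1c from both row 3 models departs from the plan's own practice in the primary analysis and in rows 1 and 2; the documents give nothing from which to size its effect. Both models are valid under randomisation. Type I error, the primary endpoint and the sample size are unaffected. This is a free improvement, not a flaw that threatens the trial.

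**What to change.** For each row 3 outcome, specify one mixed model for the change with these terms: baseline value of the index, group, time point, group-by-time, and the minimisation factors eGFR, proteinuria, age and HbA1c. An index that is itself one of these factors (eGFR, HbA1c) enters once. From that model take the adjusted arm means, the between-group difference, its 95% CI and the p-value at each time point. For urinary angiotensinogen, use the same terms without time and its interaction, which is an ANCOVA at week 4. If baseline-free means are still wanted, keep them and label them as descriptive.

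The cost is a wording change in the protocol or the analysis plan, best made before the data are analysed. The four factors are already needed for allocation and for the primary ANCOVA, and the second bullet already requires the baseline values. No patients, visits or measurements are added.
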